### **10.2 Secondary study parameter(s)**

Continuous variables (FAM or SPQ, PHQ, BAI, IRI) will be presented as mean, standard deviation, and minimum and maximum number of observations. Descriptive statistics of

demographics and clinical outcomes will be compared between the experimental and control condition. The quantitative analysis of the secondary endpoints will be performed on an intention-to-treat basis following the per protocol analysis according to CONSORT recommendations and SPIRIT guidelines for reporting results (Chan 2013a, 2013b; Eysenbach et al., 2011). Comparisons will be made between and within the groups for pre- and post-measurement and follow-up. Fantasizing ability as measured by the IRI will be investigated as a moderating variable for the effectiveness of VRET (on the outcome variable, FAS or FSQ). For the analyses on continuous scales including user data, repeated measures analyses of variance (ANOVA) are used. Multiple imputation will be used in dealing with missing data, assuming this is "at random" (Brunton-Smith et al., 2014). Analyses of flights taken after ZeroPhobia Fear of Flying will be performed using Chi-Square tests to investigate the differences per group. PROCESS (Hayes, 2018) will be used for mediation analysis in SPSS version 25. Standardized effect sizes (Cohen's d) and the confidence intervals are calculated. STATA version 14 will be used for the analyses. The best static analysis procedure to perform the analyses for this RCT will be reviewed before the data is analysed.

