## SUMMARY

**Rationale:** Specific phobias, such as intense fear of flying, heights, or spiders, are the most common forms of mental health disorders worldwide. Specific phobias have a lengthy history of clinical research and very effective treatment for specific phobias using exposure therapy already exist (Wolitzky-Taylor et al., 2008). However, due to high costs, stigma, and long waiting lists, access to evidence-based therapy is currently limited. Meta-analyses on treatment effectiveness for people suffering from specific phobias have shown that Virtual Reality Exposure Therapy (VRET) is as effective as traditional forms of exposure therapy (Marino et al., 2015; Parsons and Rizzo 2008; Powers and Emmelkamp 2008; Opris et al., 2012). VRET, however, involves relatively high costs and limited accessibility, which make it prohibitive for the larger part of the population. This project capitalizes on novel technology and recent scientific advances to develop an affordable treatment modality that is available for anybody, anywhere. Specifically, we will develop and test ZeroPhobia, a self-help VRET for aviophobia and arachnophobia, delivered through a smartphone application (app) in combination with rudimentary cardboard Virtual Reality (VR) glasses. We hypothesize that ZeroPhobia is effective in reducing anxiety symptoms and is user-friendly.

**Objective:** To determine (1) the clinical effects of ZeroPhobia to reduce aviophobia and arachnophobia symptoms at post-test, (2) the clinical effects of ZeroPhobia at 3- and 12-month follow-ups, (3) the user-friendliness of the intervention, (4) if the usage intensity and/or (5) the feeling of presence influence the primary outcome of ZeroPhobia, (6) if exposure or evaluating thoughts mediate anxiety outcomes, (7) if guided VRET results in reduced participant dropout rates, and (8) whether or not ability to fantasize influences the effectiveness of VRET.

**Study design:** This project involves two randomized controlled trial (aviophobia and arachnophobia) with two arms: the intervention condition (ZeroPhobia) and a waitlist control condition.

**Study population:** For aviophobia  $n = 96$  and for arachnophobia  $n = 72$  individuals (18-65 years) who experience aviophobia or arachnophobia symptoms, respectively, will be recruited from the general population to participate in the trial.

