Research into mobile apps as a method to intervene for psychiatric disorders are promising (e.g. Donker et al., 2013; Eysenbach et al., 2011; Saeb et al., 2015). App-based mental health interventions based on e.g. CBT principles have shown to be effective in reducing mental health symptoms with within-group and between-group intention-to-treat effect sizes ranging from  $d = 0.29 - 2.28$  and  $0.01 - 0.48$  at post-test and follow-up, respectively in a review of Donker et al. (2013). Advantages are better accessibility and participant retention, real-time progress monitoring, portability, and flexibility. As far as we know, one study has investigated the effectiveness of VRET using a mobile application for fear of spiders. Results showed a reduction in anxiety levels (Piercey et al., 2012). Another study investigating VRET on a smartphone has recently found VRET to be effective at reducing spider phobia symptoms and non-inferior to traditional one-session exposure therapy (Miloff et al., 2019).

Recently, we have explored the feasibility and efficacy of ZeroPhobia: Acrophobia, a VRET delivered through a smart phone app using Google cardboards for fear of heights (Donker et al., 2019). The randomized controlled trial (RCT) demonstrated large effect sizes and ZeroPhobia: Acrophobia was rated user-friendly. The aim of the proposed project is to test a (similar) low cost, scalable, and evidence-based solution for aviophobia and arachnophobia symptoms through exposure therapy by integrating VR technology with a smart phone app in two separate RCTs. Both interventions will be tested for its effectiveness in reducing anxiety symptoms and user-friendliness. ZeroPhobia: Arachnophobia will differ

from ZeroPhobia: Aviophobia in that it will be a guided VRET, in order to determine whether drop-out rates are lower than previous, unguided trials of ZeroPhobia. The study will be of a randomized controlled trial (RCT) design and will be conducted amongst adults from the general Dutch populations with aviophobia and arachnophobia symptoms.

We hypothesize that both ZeroPhobia applications will effectively reduce anxiety symptoms as well as be rated as user friendly.

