## **2. OBJECTIVES**

Primary Objective: To determine the clinical effects (a reduction in anxiety symptoms – aviophobia and arachnophobia at post-test [between the experimental condition and controls]) of ZeroPhobia, and whether effects are sustainable at 3- and 12-month follow-up (a reduction in anxiety symptoms between baseline and follow-up for those in the experimental condition)

Secondary Objective(s): To determine the user-friendliness of ZeroPhobia, if it is effective in reducing depression and anxiety, to determine whether usage intensity and presence in the VR environment influences the effects of ZeroPhobia, to determine whether exposure or evaluating thoughts mediate anxiety outcomes, to determine whether or not guided VRET is related to reduced participant drop-out rates, and whether ability to fantasize influences the effectiveness of VRET.

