### **8.1.3 Other study parameters (if applicable)**

- Demographic variables (gender, age, education level, marital status, employment status).
- System Usability Scale (SUS; Bangor et al., 2008): 10 items about user friendliness of the app. The SUS is composed of 10 statements that are scored on a 5-point scale of strength of agreement. Final scores for the SUS can range from 0 to 100, where higher scores indicate better usability. This means that products that are at least passable have SUS scores above 70, with better products scoring in the high 70s to upper 80s. Truly superior products score better than 90. Products with scores less than 70 should be considered candidates for increased scrutiny and continued improvement and should be judged to be marginal at best. Reliability is good (Bangor et al. 2008). This questionnaire will be completed at post-test.
- User-friendliness of ZeroPhobia as a treatment will be in part measured with the 6-item self-report treatment expectation and satisfaction scale called the

Credibility/Expectancy Questionnaire (CEQ; Devilly & Borkovec, 2000). The CEQ measures expectations of the participants before the start of the treatment. This questionnaire will be used alongside the post-test SUS and NEQ to determine if ZeroPhobia did in fact meet expectations.

- User-friendliness will also be measured using single item questions directly asking about the user experience of ZeroPhobia and the realism of the VR environments. This also includes one open question asking for any other feedback on the app a participant would like to give.
- Igroup Presence Questionnaire (IPQ; Schubert, Friedmann and Regenbrecht 2001), a 14-item questionnaire, which assess realism and “presence” in the VR environment. Each of the items has five response categories from fully disagree (1) to fully agree (5). Chronbach`s alpha is good ( $\alpha = .73$ ). This questionnaire along with some open questions about user experience of the VR environment will be completed at post-test.
- Ecological Momentary Assessment: One question about current anxiety level during exposure in VR
- Usage data from the ZeroPhobia app: frequency and duration of practice during exposure in VR, frequency and duration of time spent in the modules.
- Flight usage questions, including when was the last time you flew on an airplane, how many times have you flown in the past 3/12 months and how long was each of these flights?

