If in the intervention condition, the research assistant will send the VR glasses to the participant by postal delivery, along with usage instructions. The research assistant will email the participant with instructions on how to download the ZeroPhobia app to his/her smartphone. The app is locked with an individual code which will be given to the participant at the start of the intervention. Participants can then begin the ZeroPhobia intervention which they can follow for 6 weeks (5-20 minutes per week, in addition to VRET from module/week 3 onward, which we recommend 10 minutes a day of practice with). When practicing in VRET, participants are asked to fill in one question about their anxiety level before, during, and after VRET (duration: 5 seconds). Participants can follow the intervention at their own pace. Participants will receive weekly automatic reminder emails to begin or continue the intervention from the research assistant. If needed (e.g., with a question about how to use ZeroPhobia or in the unlikely case of distress), participants will be invited to contact the research assistant.

If in the wait-list condition, the participant will be informed that after a six week pause and the completion of a post-test assessment, they can begin the ZeroPhobia program. The wait-list group will undergo the same program procedure as those in the treatment condition. Participants of both conditions will begin the program on the first working Monday after

completing the baseline and being randomized to a condition, meaning participants of both groups will have different start and end times. Both groups will have the same duration of each section, however (see flowchart).

The aforementioned post-test (occurring after 6 weeks of either intervention or pause, or after the completion of module six in the intervention group (for those participants who choose to work through the ZeroPhobia program faster) consists of the FAS and FAM (aviophobia) or FSQ and SPQ, (arachnophobia), PHQ, BAI, IPQ, SUS, CEQ and NEQ, questions regarding whether they received professional treatment during this time, and questions about flight usage (duration: 25 minutes). Two reminders will be given across two weeks to fill in post-test, the first being an e-mail and the second a phone call.

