### **10.3 Other study parameters**

Continuous variables (IPQ, SUS, CEQ, NEQ) will be presented as mean, standard deviation, and minimum and maximum number of observations. Categorical variables will be presented in terms of frequency numbers and percentages (e.g. demographic variables). Descriptive statistics of demographics and clinical outcomes will be compared between the experimental and control condition. The quantitative analysis will be performed on an intention-to-treat basis following the per protocol analysis according to CONSORT recommendations and SPIRIT guidelines for reporting results (Chan 2013a, 2013b; Eysenbach et al., 2011). For the analyses on continuous scales including user data, repeated measures analyses of variance (ANOVA) are used. Multiple imputation will be used in dealing with missing data, assuming this is "at random" (Brunton-Smith et al., 2014). STATA version 14 will be used for the analyses. The best static analysis procedure to perform the analyses for this RCT will be reviewed before the data is analysed.

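### Section 10 puts once-only and app-dependent scales through repeated-measures and imputation methods, CEQ timing conflicts, and the mediation and guidance claims go beyond what was randomised

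*Protocol*

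**What the plan says.** **Mediation.** Section 2 sets the aim "to determine whether exposure or evaluating thoughts mediate anxiety outcomes". Section 10.2 answers that PROCESS "will be used for mediation analysis in SPSS version 25", without naming predictor, mediator variables or analysis set. Section 8.1.3 lists "Usage data from the ZeroPhobia app: frequency and duration of practice during exposure in VR", and section 12.1 lists the thought-evaluation exercise among the app data. Table 1 contains no questionnaire on thoughts. Section 3 gives the waitlist the intervention only after post-test, and section 8.3 gives the 3- and 12-month follow-ups only to the intervention arm.

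**Other scales.** Section 10.3 opens with IPQ, SUS, CEQ and NEQ as its continuous variables, plans means and standard deviations, and then adds intention-to-treat, multiple imputation and this: "For the analyses on continuous scales including user data, repeated measures analyses of variance (ANOVA) are used". Table 1 places IPQ, SUS and NEQ at post-test only and CEQ at baseline only. Section 8.3 describes one post-test, taken after six weeks of either intervention or waiting, whose list includes "PHQ, BAI, IPQ, SUS, CEQ and NEQ".

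**CEQ.** Section 8.1.3 defines it as a measure of expectations before treatment. The baseline lists in sections 8.3 and 11.2 omit it.

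**Guidance.** Section 5.1 makes the arachnophobia app guided and the aviophobia app unguided. Section 1 gives the reason: "in order to determine whether drop-out rates are lower than previous, unguided trials of ZeroPhobia". The summary states the objective as "7) if guided VRET results in reduced participant dropout rates", whereas section 2 asks only whether the two are related.

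**The concern.** Several secondary objectives depend on data that exist in only one arm, at only one time point, or in only one trial. A statistical analysis plan can refine a method, but it cannot create measurements that the schedule does not collect or a contrast that was not randomised.

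Three consequences follow if the text is carried out as it stands:

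- Waitlist participants may rate the presence and usability of an app and a VR environment they have never opened. If they leave these blank, imputation would supply values for something that has no true value in them.
- An association between app use and improvement, which motivation alone could produce, may be reported as the mechanism of the treatment effect.
- A difference in drop-out between trials of different phobias may be reported as caused by guidance.

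**Working it through.** **1. The plan's own figures.** No sample size or precision is stated for these analyses. The stated sizes concern the between-arm comparison of means. At two-sided 0.05 and 80% power, the t-test solution is 33.02 per arm for d = 0.70 and 25.52 for d = 0.80. Rounded up, these give the protocol's 34 and 26. They say nothing about the secondary questions.

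**2. Schedule against analysis.**

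| Scale | Table 1 | Section 8.3 | Section 10.3 |
|---|---|---|---|
| IPQ | post-test | post-test, no split by arm | ITT, imputation, repeated-measures ANOVA |
| SUS | post-test | post-test, no split by arm | same |
| NEQ | post-test | post-test, no split by arm | same |
| CEQ | baseline | post-test, absent from baseline list | same |

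One time point gives no within-person factor, so repeated-measures ANOVA has nothing to estimate for any of the four. Listing CEQ at post-test does not help, because Table 1 and section 8.3 then disagree about which single occasion applies.

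**3. What a mediation model would return if arm is the predictor.** Let X be arm, M app use and Y the post-test score.

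- a-path: M = a0 + aX. With M = 0 in every control, a is the mean use in the intervention arm.
- b-path: Y = i + c'X + bM. With X in the model, b pools the within-arm slopes, each weighted by the within-arm variation in M. That variation is zero in controls, so b is the intervention-arm slope alone.
- In two simulated data sets the pooled b and the intervention-arm slope were identical: 0.1009 and 0.1009; -0.2479 and -0.2479.

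The indirect effect is therefore mean use multiplied by a non-randomised slope.

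**4. How misleading this can be (illustration; the inputs are assumptions).** Take 48 per arm and a direct effect of -0.70 in residual-SD units. App use has no causal effect. A confounder C with variance 1 raises use by one unit per SD and lowers the outcome by g per SD. Use has mean 3 and added noise of variance 1, truncated at zero.

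- Expected slope, ignoring truncation: -g / (1 + 1). With g = 0.5 this is -0.25.
- Expected indirect effect: 3 x (-0.25) = -0.75. At half that confounding (g = 0.25) it would be 3 x (-0.125) = -0.375. With none it is 0.
- Simulation, 4,000 runs: with g = 0.5 the mean indirect effect was -0.75 and the b-path was significant in 57% of runs. With g = 0 the figures were 0.007 and 5%.

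With g = 0.5, an inert mediator is credited with the whole treatment effect.

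**5. Precision of the within-arm alternative.** Intervention arms are 48 and 36. After the protocol's 40% drop-out, 48 x 0.6 = 28.8 (about 29) and 36 x 0.6 = 21.6 (about 22). The smallest correlation detectable with 80% power is r = tanh[(1.960 + 0.842)/sqrt(n - 3)].

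| Trial | No drop-out | After 40% drop-out |
|---|---|---|
| Aviophobia | n = 48: r = 0.39 | n = 29: r = 0.50 |
| Arachnophobia | n = 36: r = 0.45 | n = 22: r = 0.57 |

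**6. Guidance.** Within each trial every participant has the same guidance status. Guided against unguided is therefore always one trial against another, with different phobia and app, and against earlier trials also a different period. No covariate adjustment can separate guidance from trial.

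**The case against.** - **The mediation model is not spelled out.** This is true: section 10.2 does not say that arm is the predictor, and a model within the intervention arm would fit its wording. A reader might infer that the protocol commits itself to a faulty arm-based model, and the text does not support that. What stands is that either version rests on the same within-arm slope. Non-randomised b-paths are common to mediation analyses, but here the control arm contributes nothing to that path.
- **Descriptive reporting is already planned, and usage can be repeated over time.** Both are correct. The ANOVA sentence has a possible use for app logs, but in a section whose named continuous variables are the four once-only scales it needs limiting.
- **Section 8.3 gives a combined list, and the flow chart is not available here.** The list does not say outright that controls complete IPQ and SUS. It gives no exemption either, and it describes the post-test as following intervention or waiting.
- **Usability.** A reader might infer that the user-friendliness objective also fails. It does not: it needs only users, and section 8.1.3 supplies a SUS benchmark of 70.
- **NEQ.** A reader might wish to drop it for controls. Its items can be attributed to circumstances other than treatment (section 8.1.3), so controls can answer it and provide the only concurrent comparison.
- **Guidance.** A reader might infer a flawed planned test. Section 10 contains none, and section 2 is worded as an association. Power computed for the two current trials against each other would not address section 1, which names previous unguided trials as comparator.
- **Method review before analysis.** The protocol allows this, but it changes neither the schedule nor the objectives.

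**Conclusion.** The point holds in four parts:

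1. Repeated-measures ANOVA cannot apply to IPQ, SUS, CEQ or NEQ as scheduled. Intention-to-treat with imputation has no meaning for IPQ and SUS in controls who have used neither app nor VR.
2. CEQ timing is contradictory between section 8.1.3 and Table 1 on one side and sections 8.3 and 11.2 on the other.
3. Exposure, thought evaluation, usage and presence exist before post-test only in the intervention arm. They support confoundable within-arm associations, not mediation or modification of the randomised effect.
4. The summary's causal wording on guidance and drop-out has no randomised basis.

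Part 3 assumes that the mediators are the app data named in sections 8.1.3 and 12.1; the protocol lists no other source. The simulated -0.75 and 57% depend on the assumed confounding and usage distribution and show what can happen, not what will. Moderation by IRI is not affected, because fantasy ability is a baseline measure in both arms.

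**What to change.** - **Section 8.3:** exempt the waitlist from IPQ and SUS at post-test, and move CEQ to baseline before randomisation, in line with Table 1. Add CEQ to the baseline list in section 11.2.
- **Section 10.3:** report IPQ and SUS descriptively in the intervention arm, with SUS set against the stated benchmark of 70. Do not impute either for controls. Remove repeated-measures ANOVA for scales taken once. Keep NEQ in both arms as a comparison at a single time point.
- **Section 10.2:** analyse usage, exposure, thought exercises and presence within the intervention arm, as baseline-adjusted associations with post-test FAS or FSQ, and make no claim of mediation. State the expected precision.
- **Summary and section 2:** align summary objective 7 with the associational wording of section 2, and report drop-out in the guided trial descriptively with a 95% confidence interval. Reword the mediation objective as an association.

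The cost is wording changes and weaker claims about mechanism and guidance. No participants or visits are added, and the waitlist post-test becomes shorter. Only fairly strong within-arm associations will be detectable, and the report should say so.

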### **10.3 Other study parameters**

Continuous variables (IPQ, SUS, CEQ, NEQ) will be presented as mean, standard deviation, and minimum and maximum number of observations. Categorical variables will be presented in terms of frequency numbers and percentages (e.g. demographic variables). Descriptive statistics of demographics and clinical outcomes will be compared between the experimental and control condition. The quantitative analysis will be performed on an intention-to-treat basis following the per protocol analysis according to CONSORT recommendations and SPIRIT guidelines for reporting results (Chan 2013a, 2013b; Eysenbach et al., 2011). For the analyses on continuous scales including user data, repeated measures analyses of variance (ANOVA) are used. Multiple imputation will be used in dealing with missing data, assuming this is "at random" (Brunton-Smith et al., 2014). STATA version 14 will be used for the analyses. The best static analysis procedure to perform the analyses for this RCT will be reviewed before the data is analysed.

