- Professional treatment (medication and other psychiatric treatment) will be asked during the screening process, but also at post-test and follow up timepoints in order to control for possible other therapeutic effects.
- Negative Effects Questionnaire (NEQ; Rozental et al., 2016) consists of 32 questions and will be used to assess side effects of psychological treatments. Each question can be answered either ‘yes’ or ‘no.’ If yes, participants are then asked to rate how negative the experience of this item was on a 5-point Likert scale (from ‘not at all’ to ‘extremely’). Participants are then asked to determine whether this experience was probably caused by ‘the treatment that I am undergoing’ or ‘other circumstances.’ The NEQ has been found to have good validity (Rozental et al., 2019).

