| CEQ                                               | To determine program's user-friendliness                                            | x |   |   |
| NEQ                                               | To determine whether there are any negative effects of ZeroPhobia                   |   | x |   |
| IPQ                                               | VR experience                                                                       |   | x |   |
| IRI                                               | To determine influence of fantasizing ability on effectiveness of VRET              | x |   |   |
| WSQ                                               | To control for confounding variables                                                | x |   |   |
| Flight usage                                      | To determine effectiveness of treatment                                             | x | x | x |
| General flight anxiety questions                  | To further understand the type of flight anxiety a participant has                  | x |   |   |
| User-friendliness and realism questions           | To further understand the user experience of the ZeroPhobia app and VR environments |   | x |   |
| Professional treatment (medication and treatment) | To control for confounding variables                                                | x | x | x |

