## **10. STATISTICAL ANALYSIS**

### **10.1 Primary study parameter(s)**

The primary outcome measure (FAS for aviophobia, FSQ for arachnophobia) will be treated as a continuous outcome. Continuous variables will be presented as mean, standard deviation, and minimum and maximum number of observations. Descriptive statistics of demographics and clinical outcomes will be compared between the experimental and control condition. The quantitative analysis of the primary endpoints will be performed on an intention-to-treat basis following the per protocol analysis (PPA) according to CONSORT recommendations and SPIRIT guidelines for reporting results (Chan 2013a, 2013b; Eysenbach et al., 2011). Comparisons will be made between and within the groups for pre- and post-measurement and follow-up. Multiple imputation will be used in dealing with missing data, assuming this is "at random" (Brunton-Smith et al., 2014). We will calculate Clinical Meaningful Change on the FAS (Evans, 1998) and a reliable change criterion (Evans, 1998). We will also calculate the number needed to treat (NNT) based on (Christensen et al., 1986; Cohen, 1972). Standardized effect sizes (Cohen's d) and the confidence intervals are calculated. STATA version 16 will be used for the analyses. The best static analysis procedure to perform the analyses for this RCT will be reviewed before the data is analysed.

Intention-to-treat analysis will be used on continuous scales using repeated measures analysis of variance (ANOVA). Per protocol analysis will be performed by independent sample t-tests. Standardized effect sizes (Cohen's d) and confidence intervals will be calculated. SPSS version 21 will be used for the analyzes. A  $p$ -value  $<0.05$  will be considered to indicate statistical significance.

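### Section 10.3 reduces the NEQ, the instrument meant to detect negative effects of the app, to a mean score with a repeated measures ANOVA that cannot be run over time, and plans no treatment-attributed count or interval.

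*Protocol*

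**What the plan says.** Table 1 (Protocol Section 8.3) gives the NEQ a single aim: "To determine whether there are any negative effects of ZeroPhobia". The table marks it at post-test and at no other time.

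Section 8.1.3 describes its content. It "consists of 32 questions and will be used to assess side effects of psychological treatments". After a yes, "participants are then asked to rate how negative the experience of this item was on a 5-point Likert scale". Then comes attribution: "Participants are then asked to determine whether this experience was probably caused by" the treatment or by other circumstances.

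Section 10.3 fixes the analysis: "Continuous variables (IPQ, SUS, CEQ, NEQ) will be presented as mean, standard deviation, and minimum and maximum number of observations". It continues: "For the analyses on continuous scales including user data, repeated measures analyses of variance (ANOVA) are used". Multiple imputation is to handle missing values. Sections 10.1 and 10.2 promise confidence intervals; Section 10.3 does not.

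**The concern.** The stated summary does not answer the stated question. Whether the app has negative effects is a matter of how many users had one, how bad it was, and whether they put it down to the app. The NEQ collects all three, but a mean total keeps none of them separate. Events blamed on other circumstances count the same as events blamed on the app, and one severe effect in a few people is spread over everyone else's scores.

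The named test also does not fit. A repeated measures ANOVA over time needs at least two measurements, and the NEQ has one.

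At stake is the usefulness of the one instrument in Table 1 whose stated aim is negative effects. The trial is run at home with online assessment, Section 9.5 sets up no DSMB, and Table 1 has no cybersickness or fall measure.

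**Working it through.** **1. Sample size available.** The protocol gives no figure for the NEQ, so the only plan figures to reproduce are those of Section 4.3. A two-sided 0.05 two-sample t-test with 80% power needs 34 per arm at d = 0.70 and 26 per arm at d = 0.80, as stated. The totals follow from multiplying by 1.4: 68 × 1.4 = 95.2 (stated 96) and 52 × 1.4 = 72.8 (stated 72). With 48 and 36 per arm and 40% drop-out, expected respondents per arm are:
- aviophobia: 48 × 0.6 = 28.8, taken as 29;
- arachnophobia: 36 × 0.6 = 21.6, taken as 22 or 21.

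**2. The named test.** With one NEQ measurement there is no time factor. If both arms complete it, the comparison collapses to a two-group comparison of means, equivalent to a two-sample t-test. That is the nearest analysis that can be run, and it is used below, although Section 10.3 does not name it.

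**3. How far the mean moves.** Assumptions, none from the protocol: NEQ total with an exponential background and SD of 4, 8 or 12; harm adds 4 or 8 points in 10% of app users (4 points is one item at maximum severity if coded 0 to 4).
- Mean shift = share × points: 0.10 × 4 = 0.4 and 0.10 × 8 = 0.8 points.
- In SD units: 0.4/12 = 0.03 up to 0.8/4 = 0.20.
- Smallest standardised difference with 80% power: 0.58 (48 per arm), 0.67 (36), 0.75 (29), 0.89 (21).

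Simulation (8,000 trials per setting) gives the share of trials significant at two-sided 0.05 in the harm direction. With no effect this would be about 0.05/2 = 2.5%.

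| Per arm | 10% of users, 4 points (SD 4 / 8 / 12) | 10% of users, 8 points (SD 4 / 8 / 12) |
|---|---|---|
| 48 | 7.3 / 4.7 / 3.7% | 14.0 / 7.6 / 5.2% |
| 36 | 6.4 / 4.2 / 3.6% | 11.4 / 5.6 / 4.2% |
| 29 | 5.6 / 3.8 / 3.1% | 9.9 / 5.5 / 4.5% |
| 21 | 5.1 / 3.7 / 3.3% | 8.2 / 5.4 / 3.9% |

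For a common harm the picture changes. With 4 to 12 points in 25% of users, detection is 6% to 78% at 48 per arm and 5% to 54% at 29 per arm.

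**4. What a count with an interval would show.** For zero cases among n respondents, the exact two-sided 95% upper limit is 1 − 0.025^(1/n).

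| Trial | n in app arm | Upper limit |
|---|---|---|
| Aviophobia, all respond | 48 | 7.4% |
| Aviophobia, 40% drop-out | 29 | 11.9% |
| Arachnophobia, all respond | 36 | 9.7% |
| Arachnophobia, 40% drop-out | 22 or 21 | 15.4% or 16.1% |

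At the planned drop-out, both limits lie above 10%.

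**The case against.** **Silence is not exclusion.** Section 10.3 also says: "Categorical variables will be presented in terms of frequency numbers and percentages (e.g. demographic variables"). The example need not be exhaustive, the procedure is to be reviewed before analysis, and a statistical analysis plan may hold item and attribution tables. So a reader might infer that the attribution answers will be discarded, but the protocol nowhere says so. What remains is that the NEQ is assigned by name to the continuous list, with a test that does not fit it. A general promise of review does not correct that.

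**No rule equates non-significance with safety.** A reader might infer that a real harm would usually be reported as no negative effects. The documents do not support this. The p < 0.05 criterion that "will be considered to indicate statistical significance" stands in Section 10.1 for the primary parameters, and Section 10.3 gives no decision rule. Nor does it hold for every harm: the only harm rate in the document is 24/96 = 25% with cybersickness symptoms in the earlier acrophobia study (Section 13.1), and a 25% harm with a large effect on a low-variance score reaches 78% detection.

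**Sample size explains much of the miss.** This stands. Tested as proportions, 10% versus 2% has Fisher power of 17% at 48 per arm and 4% at 29. The chance of seeing at least one case (1 − 0.9^29 = 95%) is not comparable with the chance of a significant test.

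**Other capture exists.** This stands too. Spontaneously reported and observed adverse events are recorded (Section 9.2.1) and serious ones reported individually (Section 9.2.2). The BAI, PHQ-9 and a reliable change criterion could show symptom worsening.

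**Self-attribution is unblinded, whereas a randomised comparison deals with other causes by design.** This is fair. Section 8.3 appears to give the post-test NEQ to both arms, so all-cause frequencies by arm belong beside the attributed counts.

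**Conclusion.** The point holds in a limited form. Section 10.3 fixes a continuous summary for a yes/no, severity and attribution instrument, names an ANOVA over time for something measured once, and plans neither use of the attribution answer nor an interval. None of this answers the aim in Table 1. The insensitivity of the mean is shown only for harms in about 10% of users or fewer. It rests on assumed score distributions and on a t-test standing in for the unworkable ANOVA. The exact upper limits in step 4 depend only on the number of respondents. This is an inexpensive improvement to how harm is reported; it does not show that harm would go unnoticed.

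**What to change.** In Section 10.3:
- Remove the NEQ from the scales analysed by repeated measures ANOVA and multiple imputation.
- On observed data, report the number and proportion of app-arm respondents with at least one effect attributed to the treatment, and with at least one such effect in the top severity categories. Give exact two-sided 95% confidence intervals for both.
- Report item frequencies in the same way.
- If the waitlist arm completes the NEQ, show all-cause frequencies for both arms alongside.
- Report any zero count with its upper limit.
- Keep the NEQ total as a descriptive extra.

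The cost is a few sentences and one frequency table per trial; no new data or participants are needed. The downside is that the intervals will be wide and the safety statement less favourable. The gain is an attributed rate with its uncertainty, not a powered test of harm.
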